#### Evaluation of the structural quality

The evaluation of the structural quality is carried out on the basis of cross-sectional analyses of the available routine data. Reference data are used to evaluate the degree of achievement. In addition, primary data on structural features are collected as part of the quantitative cross-sectional survey of paediatricians. In this context, the cross-sectional design is well suited to examining the absolute and relative frequency of structural features between participating and non-participating physicians or insured persons. The structural characteristics of the physicians include, for example, region, group of specialists, size of practice, practice kind (single practice, joint practice or practice communities), number of patients treated per quarter, age and sex. Among the structural characteristics of insured persons are e.g. age, sex, nationality, income, education and occupational status (of parents) and chronic diseases (diabetes mellitus, ADHD, asthma, allergy and obesity).

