### Measurements

Within the scope of the project, the instruments for primary surveys shown in Table 1 with the parameters mentioned will be developed for the target groups. In addition, the performance and accounting data of AOK Nordost will be included in the analyses.

**Table 1 Tab1:** Survey instruments and parameters

Target group	Instrument	Parameter
Paediatricians	Structured interview guide for the focus group survey	Barriers / hindering factors, potentials / promoting factors, satisfaction
	Partially standardised questionnaire	Participation, abortion reasons, practice size/form, specialist group, age (year of birth), gender, work experience, region, working time per week, number of patients treated per quarter, proportion of private patients, satisfaction, incentives, barriers / obstructive factors, potentials / promoting factors
Children and adolescents	Structured interview guide for the focus group survey	Barriers / hindering factors, potentials / promoting factors, satisfaction, expected benefit, effort
	Partially standardised questionnaire	Age (year of birth), gender, sociodemography (income, education, migration, occupational status), region, satisfaction, barriers / hindering factors, potentials / promoting factors, expected benefit / incentives, effort, utilization of U-examinations (U8, U9), health-related quality of life (KIDSCREEN 27), health behavior, body size and weight

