For the focus group survey of the C&A, a random sample of all participants and non-participants is selected and invited from the routine data of the AOK Nordost. For the quantitative survey, a random sample of the participating and non-participating C&A is also selected from the routine data of the AOK Nordost to receive a postal questionnaire. A higher response rate can be expected among C&A than with the target group of physicians. Nevertheless, it is difficult to convince the target group to participate in the surveys. On the one hand, this was taken into account by a conservative assumption of the response rate (40%) in the case number calculation. On the other hand, in order to achieve a high level of acceptance among the target group, a joint approach was made with the BVKJ. In addition, each questionnaire contains a personal address in the form of a handwritten note, with thanks for participating [4]. Proven methods such as incentives and reminders are used to increase response rates and reduce the risk of selection bias through systematic non-participation. In addition, a target group-specific and culture-sensitive approach and linguistic translation of the questionnaire instrument for Turkish, Russian and Arab migration groups will be provided. After 2 weeks and after 4 weeks a reminder will be sent to all C&A. In addition, 30 age-appropriate incentives of max. 30 € each will be raffled off.

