**Fig. 2 Fig2:**
[figure not shown]
Flowchart for the primary survey among the target group of paediatricians based on the STROBE Statement

At the level of the C&A, all patients who have used the services are included in the IG as part of the secondary data analyses. Using PS matching, a suitable CG is drawn from the secondary data in a ratio of 1:1. The collection of primary data takes place in a sub-sample, whose case number was calculated on the basis of the primary outcome parameter of the health-related quality of life. A 2 × 3-factorial design is used to compare the intervention with standard care (IG/CG) (factor 1), taking into account multiple factors, e.g. the region (factor 2). To demonstrate expected small effects at the significance level of α ≤ 0.05 and a power of 80%, a net sample of *n* = 1096 (*n* = 548 per group) is required for analysis. With a conservatively expected response rate of 40%, a sample of *n* = 2740 is invited to participate. The case number planning and the analysis methods are selected in order to adjust for covariates (e.g. gender). The expected course of the study for the target group is shown in Fig. 3.

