#### Quantitative analyses

The data evaluations are initially performed descriptively. The hypotheses developed are also tested for inferential statistics. In order to ensure comparability between participating and non-participating insured persons, a CG is formed for the IG on the basis of the routine data using the characteristics gender, age and comparable region. Participants from both groups are brought together with PS matching at the individual level. The analyses of the primary data take into account in particular covariates for which it was not possible to match at the secondary data level, such as socio-economic status and migration background. The influence of the selective contract is checked using ANCOVA. The analyses are carried out with the software programs SAS, SPSS and Microsoft Excel.

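### Illness before enrolment appears in neither the matching set, nor the stated covariate rule, nor the questionnaire content of the quality-of-life survey, although the routine data used as its sampling frame hold dated diagnoses

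*Protocol article*

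**What the plan says.** - **Outcome and size.** Under Sample size calculation (Quantitative surveys), the survey sub-sample is sized on the "primary outcome parameter of the health-related quality of life", with 1096 respondents (548 per group) from 2740 invited.
- **Sampling frame.** Under Participant recruitment, "a random sample of the participating and non-participating C&A is also selected from the routine data of the AOK Nordost".
- **Matching.** Study population and Quantitative analyses both give the same three characteristics for the propensity score: sex, age and comparable region.
- **Adjustment.** Quantitative analyses says the primary-data analyses pay particular attention to "covariates for which it was not possible to match at the secondary data level, such as socio-economic status and migration background", and that the influence of the contract is checked by ANCOVA. The sample size section adds gender as an example of a covariate.
- **Questionnaire content.** The children's row of Table 1 (Measurements) covers sociodemography, satisfaction, use of U8 and U9, and "health-related quality of life (KIDSCREEN 27), health behavior, body size and weight". It lists no chronic-illness parameter.
- **What is known about illness.** Evaluation of the structural quality lists "chronic diseases (diabetes mellitus, ADHD, asthma, allergy and obesity" among the characteristics of insured persons. The outcome-quality section takes the time of detection and the incidence of chronic disease from the routine data, so those data must hold dated diagnoses.
- **Design.** The same section describes the surveys as cross-sectional.

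**The concern.** This is a non-randomised comparison with voluntary enrolment, and the plan handles confounding in two steps: match on what the routine data offer, then adjust for what they could not offer. Prior illness falls between the steps. It is not among the three matching variables. Because the routine data do contain diagnoses, it is also not something that could not be matched on. Table 1 does not collect it, and a cross-sectional survey has no baseline score to absorb a difference at entry.

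Unequal illness is plausible from the article itself. Two modules are for children who already have a condition (immunotherapy support in allergic rhinitis and the target agreement on overweight), which gives their families a reason to join. More engaged families with healthier children might equally be the ones who join. In the first case a useful programme could look useless or harmful; in the second, an ineffective one could look beneficial. Since the survey is planned for a small effect, even a modest bias is large relative to it.

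**Working it through.** **1. The plan's own figure.** The plan states: "To demonstrate expected small effects at the significance level of α ≤ 0.05 and a power of 80"%. No numerical effect size is given. Assume Cohen's f = 0.10, which is d = 0.20 for two groups. Noncentral-F power with 3 numerator degrees of freedom gives N = 1095, against the stated 1096. The invited sample also reproduces: 1096 / 0.40 = 2740.

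**2. Precision of the group comparison.** In SD units, unadjusted, with 548 per group:

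- SE = √(2/548) = 0.0604
- difference detectable with 80% power at two-sided 5% = (1.96 + 0.84) × 0.0604 = 0.169 SD
- power for d = 0.20 on the two-group contrast = 91%

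**3. Bias from unequal illness.** Bias = (difference in illness prevalence between groups) × (effect of illness on quality of life, in SD). The prevalence difference is the one remaining after the planned matching and adjustment. With no true effect, and r = bias / SE, the chance of a significant result is Φ(r − 1.96) + Φ(−r − 1.96).

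The article gives neither input, so both are assumed:

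| Prevalence difference | Effect 0.2 SD | Effect 0.5 SD | Effect 0.8 SD |
|---|---|---|---|
| 5 points | bias 0.010, 5.3% | bias 0.025, 7.0% | bias 0.040, 10.2% |
| 10 points | bias 0.020, 6.3% | bias 0.050, 13.1% | bias 0.080, 26.3% |
| 20 points | bias 0.040, 10.2% | bias 0.100, 38.0% | bias 0.160, 75.4% |

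The percentages are false-positive rates against a nominal 5%. Worked example (10 points, 0.5 SD): r = 0.05 / 0.0604 = 0.83; Φ(−1.13) + Φ(−2.79) = 0.129 + 0.003 ≈ 0.13.

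**4. Effect on power if participants are the sicker group.** For a true benefit of 0.20 SD and a bias of −0.05 SD, the expected difference is 0.15 SD, and 0.15 / 0.0604 = 2.48. Power is Φ(2.48 − 1.96) ≈ 70% instead of 91%. For a true benefit at the detectable limit of 0.169 SD, the same bias takes power from 80% to 51%.

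**5. Cost in sample size of adjusting.** Adding one to three covariates to the calculation in step 1 leaves N at 1095, apart from any collinearity between illness and group.

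**The case against.** The strongest reply is that the covariate list is open. The article presents socio-economic status, migration background and gender as examples, and a full list of ANCOVA terms normally belongs in the analysis plan. A reader might infer that the plan rules out adjusting for illness. The text does not support that: illness is omitted, not excluded. What remains is that the article does fix a matching set, a rule for choosing survey covariates and the questionnaire content, and following all three as written leaves illness out.

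Other points that stand, at least in part:

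- **Weight of the outcome.** A reader might take this for a flaw in the main comparison. It is not. None of H1 to H5 concerns quality of life, which is primary only for sizing the survey; earlier detection is assessed from routine data.
- **Availability.** It is tempting to say that the project already holds this covariate for every respondent. The article says the sample is drawn from routine data, but not that answers are linked to individual diagnoses.
- **Table 1.** It lists parameters of instruments still to be developed, so an illness item could yet be added.
- **Plausibility.** The additional check-ups and the eye and skin checks are offered by age, not for existing illness, so enrolment need not favour sick children.
- **Magnitude.** All prevalences and effects of illness are assumed, and small imbalances do little harm: 5 points at 0.5 SD gives 7%.

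**Conclusion.** The concern holds in a limited form. Illness before enrolment is a direct determinant of quality of life, the sampling frame contains it, and none of the three stated places (matching, covariate rule, questionnaire content) takes it up. With voluntary enrolment and no baseline score, a difference in illness at entry would be attributed to AOK-Junior.

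Neither the direction nor the size can be established from the article. With an assumed effect of illness of 0.5 SD, imbalances of 5, 10 and 20 points correspond to biases of 0.025, 0.05 and 0.10 SD and false-positive rates of about 7%, 13% and 38%. The last bias is half of an assumed small effect of d = 0.20. These figures show how sensitive the survey would be; they do not predict what will happen. The point is worth correcting before the survey sample is drawn, and it does not bear on the detection and cost hypotheses.

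**What to change.** Take the diagnoses listed under Evaluation of the structural quality, as recorded before enrolment (for controls, before the matched age and calendar date), and use them in one of these ways:

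1. **At sampling.** Add them to the propensity score when the survey sample is drawn. This needs no linkage of answers to diagnoses, though it balances those invited, not necessarily those who reply.
2. **In the analysis.** Where families consent to linkage, enter them as covariates in the quality-of-life ANCOVA. The required sample size does not change.
3. **In the questionnaire.** If neither is possible, add one item on chronic illness with year of diagnosis.

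Use pre-enrolment illness only. The programme is meant to bring diagnoses forward, so adjusting for later ones could remove part of its effect.

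**Cost.** Controls need an assigned index date, and a line in the consent text or one extra item may be required. For children enrolled from birth there is little to adjust for, so the gain is mainly in those who joined later.

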#### Health economic analyses

Within the scope of a complete health economic evaluation, the incremental costs are related to the incremental effects. In addition, determinants for achieving an appropriate cost-effectiveness ratio are examined.

## Discussion

The project provides information on the extent to which secondary prevention measures can lead to early detection of diseases and a reduction in unhealthy behaviour. Furthermore, the evaluation shows potentials and barriers during the implementation of the selective contract. For the first time, a cost analysis enables more concrete assessments of the implementation of future prevention measures, the reduction of childhood and youth specific diseases and creates a basis for future decisions and investments in the areas of health promotion and prevention. In addition, determinants for achieving an appropriate cost-effectiveness ratio are investigated. The evaluation results are expected to provide indications for the further development of the selective contract,for which recommendations for action will be derived.

The aim is to make the results and concrete recommendations available to the implementing actors. Thus, the gap in health care provision for C&A should be closed and the quality of prevention, early detection and prevention improved. The evaluation project can contribute to reducing the misuse, underuse or overuse of health care services and to meeting the needs and demands of C&A. An extension of selective contractual services or care approaches to standard care can also increase patient satisfaction.

## Data Availability

Not applicable.

## Abbreviations

AOK: Allgemeine Ortskrankenkasse (Health Insurance Fund)
BVKJ: Berufsverband der Kinder- und Jugendärzte (Professional Association of Paediatricians and Adolescent Physicians)
C&A: Children and adolescents
CG: Control group
IG: Intervention group
